### Trial population and eligibility

All TBI patients presenting to participating hospitals are potentially eligible for this trial. The inclusion criteria are (1) age > 18 years, (2) clinical diagnosis of TBI with GCS < 13 on admission (with visible intracranial pathology on CT), and (3) invasive intracranial pressure monitoring by intra-parenchymatous transducer or ventricular catheter placement and management of increased ICP for at least 24 h. The exclusion criteria are (1) a clear, non-traumatic cause of low GCS on admission (e.g., toxic or cardiac cause); (2) not expected to survive more than 24 h after admission with the decision to abstain from aggressive treatment and induce palliative care; (3) brain death on arrival in the participating centers; (4) severe pre-trauma disability, defined as being dependent on other people; (5) known prior history of sensitivity to blood products or C1-INH; (6) patients with a history of hereditary angioedema (if known at admission); (7) patients with a history of thrombosis (deep vein thrombosis, cerebral venous sinus thrombosis, or pulmonary embolism) (if known at admission); and (8) patients that are pregnant (if known at admission).

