### Randomization

Patients in the trial are allocated to treatment with C1-INH or placebo in a 1:1 ratio, via a confidential interactive web-based algorithm software (Castor EDC, Ciwit B.V., Amsterdam, The Netherlands) using permuted block sized with stratification by study center. Randomization will be performed by the treating neurosurgeon, neurosurgical resident, or research physician after obtaining informed/deferred consent. An automatically generated email will be sent to the pharmacy with information regarding treatment allocation after randomization through Castor EDC.

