### Secondary endpoints

Secondary endpoints include all-cause mortality rate during the study period (proportion), ICP burden (pressure and time dose (PTD) calculated as the area under the curve above ICP threshold of 20 mmHg) during ICP monitoring, occurrence of CT midline shift during hospitalization (proportion), ICU and hospital length of stay (median), and hospital discharge location (proportion). Additionally, the GOSE will be assessed at discharge and 3 and 12 months follow-up. Quality of life will be assessed using the Quality of Life after Brain Injury Scale (QoLiBri) [45, 46]. The QoLiBri is the first TBI disease-specific quality of life outcome tool that is cross-culturally developed and validated in large populations. This questionnaire consists of 37 items designed to assess the health-related quality of life (HRQol) after TBI, and the median score will be compared at 3, 6, and 12 months after trauma. To assess health and well-being, the Short Form (SF)-36 [47] and 5-Level EuroQol 5-Dimensional Questionnaire (EQ-5D-5L) will be assessed [48]. SF-36 is a subjective measure of health and well-being, and the median score will be compared at 6 and 12 months after head trauma. The EQ-5D-5L is a 5-dimensional generic instrument assessing health-related quality of life and health status and generates an index of health. This questionnaire will be filled out by patients at 6 and 12 months follow-up, and the median score will be compared between the groups. The cost-effectiveness of the C1-INH will be analyzed with the median costs per quality-of-life year (QALY), based on the iMTA Productivity Cost Questionnaire (iPCQ) and iMTA Medical Consumption Questionnaire (iMCQ) at 3, 6, and 12 month follow-up [49]. Blood and CSF samples will be used (up to 96 h after C1-INH administration) to measure complement activation in an exploratory fashion, using WIESLAB, C4b/C, C3b/C, and C5b-9 ELISA assays. Neurological damage will be analyzed with glial fibrillary acidic protein (GFAP) and ubiquitin C-terminal hydrolase-L1 (UCHL-1) biomarkers. To explore the interactions of the complement system with the coagulation cascade, routinely, PT, aPPT, PLT, d-dimer, and fibrinogen tests will be performed and compared between the treatment groups. The Disseminated Intravascular Coagulation (DIC) Score will be calculated for all patients as proposed by the Scientific and Standardisation Committee of the International Society on Thrombosis and Haemostasis [50]. Lastly, general inflammatory markers, TNF-alpha, and interleukins will be analyzed to explore the effect of C1-INH on neuroinflammation.

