
### Sample size

To detect a between-group difference in the TIL Scale of 2.2, with 90% power and 0.05 (two-sided) significance level, a total of 106 patients are required. Calculations were based on the anticipated mean of 8.2 and standard deviation 3.2 of the novel TIL in TBI patients admitted to the ICU [38]. The patient group treated with C1-INH is estimated to have an average TIL of 6 [39, 51]. Both treatment groups will include 53 patients to power the trial and to account for withdrawal and loss to follow-up (approximately 10%). With this sample size, a difference of 2.2 on the TIL scale can be detected, which is clinically relevant as it corresponds to one medium level of intervention (such as CSF drainage or mannitol treatment) less to control ICP indicating a significant treatment effect. As no minimal clinically important difference (MCID) for the TIL scale is defined in the literature, we will adhere to this shift of 2.2 points on the right-skewed scale.

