### Statistical analysis

The trial profile will be summarized using a Consolidated Standards of Reporting Trials (CONSORT) flow diagram, including the reasons for non-eligibility and non-enrollment [52]. The data will be analyzed on an intention-to-treat basis with all randomized patients included in the analysis. Baseline variables will be summarized using descriptive statistics. In line with the IMPACT recommendations, the investigators plan to analyze the primary outcome TIL by using a linear model with covariate adjustment for age, GCS, and pupillary reactivity to adjust for baseline imbalances and to optimize statistical efficiency [53]. TIL will be analyzed as the TILmax for each patient, and the median for each group will be calculated. The treatment effect estimated will be based on the adjusted mean differences including 95% confidence intervals. To maintain the 5% familywise error rate, while still comparing the multiple clinically relevant endpoints, we will use a serial gatekeeping approach for statistical testing [54]. Analysis of GOSE at 6 months, as an ordinal outcome, will be done only if a significant difference in TIL is found. The co-primary endpoint GOSE will not primarily be used to declare the study success. For the analysis of GOSE at 6 months, covariate adjustment for the strongest predictors of outcome in TBI will be performed as mentioned above. The effect estimate will be an adjusted proportional odds ratio with 95% confidence interval for the shift in the direction of a better outcome on the GOSE. The ordinal regression model assumes that the odds ratio for each potential cut of the GOSE is constant no matter which cutoff point is taken (proportional odds assumption). Although the common odds ratio is formally only valid if the proportional odds assumption is met, the common odds ratio can be interpreted as a summary measure of treatment effect, even if the odds ratios differ by cutoff [55, 56]. In this study, the resulting single, common odds ratio can be interpreted as the average shift over the GOSE scale at 6 months caused by C1-INH compared to placebo [56].

Secondary analyses will be compared between the treatment groups using unadjusted and adjusted (ordinal) logistic and linear regression. Time-to-event analyses will be undertaken using Kaplan-Meier curves, as well as Cox proportional hazards regression models.

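### Neither efficacy model adjusts for mass effect on the entry CT: the covariate set is valid, but a modest and cheap efficiency gain goes unused

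*Protocol article*

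**What the plan says.** The Statistical analysis section of the protocol article fixes a linear model for TILmax with three covariates: age, GCS and pupillary reactivity. It gives two reasons for adjusting, namely to deal with baseline imbalance and to gain efficiency, and it cites the IMPACT recommendations. For the ordinal co-primary endpoint it says: "For the analysis of GOSE at 6 months, covariate adjustment for the strongest predictors of outcome in TBI will be performed as mentioned above". The only covariates mentioned above that sentence are the same three, so both efficacy models share one set and no CT variable is in it.

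CT appears in two other places. Under Trial population and eligibility, the second inclusion criterion requires a GCS below 13 "with visible intracranial pathology on CT". Under Secondary endpoints, midline shift on CT is an outcome, counted as the proportion of patients in whom it occurs during the hospital stay. The Ethics section places the eligibility check at insertion of the ICP monitor, within 12 hours of trauma.

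**The concern.** If visible pathology on CT is needed for entry, every eligible patient should have been scanned before randomisation. Everyone enrolled has some pathology, so its presence carries no information, but the degree of mass effect can still differ between patients. Midline shift on that scan is a plausible predictor of how much ICP-directed treatment a patient needs, which is what TIL scores, and of the six-month outcome. None of the three chosen covariates measures it directly.

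Randomisation is stratified by centre only, so the model is the one place where a chance imbalance in mass effect could be adjusted for. The stakes are efficiency: a somewhat wider interval for the TIL difference, and lower power for GOSE, an endpoint for which the article gives no power calculation.

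**Working it through.** **Step 1. The plan's own sample size.** Inputs from the Sample size section: difference 2.2, SD 3.2, two-sided 0.05, 90% power, about 10% loss; stated total 106 (53 per arm).

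- Normal approximation: n = 2 × (1.960 + 1.282)² × (3.2/2.2)² = 2 × 10.51 × 2.116 = 44.5, so 45 per arm. With loss, 45/0.9 = 50 per arm, 100 in total.
- Exact two-sample t: 46 per arm. With loss, 46/0.9 = 51.1, so 52 per arm, 104 in total. This is within two patients of 106.

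The SD of 3.2 is unadjusted, so the calculation takes no credit for covariates. With 53 × 0.9 ≈ 48 evaluable per arm and no adjustment at all, power is 91.5%; with all 53 it is 93.9%. Leaving CT out therefore does not threaten the stated 90%.

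**Step 2. TIL with CT added.** The article gives no R-squared for any covariate. Assume that age, GCS and pupils explain R₀ = 0.10 and that CT adds R_CT between 0 and 0.20.

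- Residual SD = 3.2 × √(1 − R₀ − R_CT)
- SE ratio = √[(1 − R₀ − R_CT)/(1 − R₀)]
- 95% CI half-width = t(0.975; 90) × residual SD × √(2/48)

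Example, R_CT = 0.10: residual SD = 3.2 × √0.80 = 2.862; SE ratio = √(0.80/0.90) = 0.943; half-width = 1.987 × 2.862 × 0.2041 = 1.16.

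| R_CT | SE ratio | CI half-width, 48 per arm | Power, 48 per arm |
|---|---|---|---|
| 0 | 1.000 | 1.23 | 94.0% |
| 0.02 | 0.989 | 1.22 | 94.5% |
| 0.05 | 0.972 | 1.20 | 95.1% |
| 0.10 | 0.943 | 1.16 | 96.1% |
| 0.20 | 0.882 | 1.09 | 97.9% |

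Expressed as sample size, a partial correlation r is worth a factor 1/(1 − r²): 1.00 at r = 0, 1/0.96 = 1.04 at r = 0.2, 1/0.84 = 1.19 at r = 0.4.

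**Step 3. GOSE with CT added.** Proportional-odds simulation, 96 patients, 3,000 trials per scenario. Assumed GOSE probabilities: 0.30/0.02/0.18/0.08/0.12/0.10/0.10/0.10. A score standing for the three existing covariates has coefficient 1.0 per SD in both models.

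| CT odds ratio per SD | Treatment OR | Power without CT | Power with CT | Gain (points) |
|---|---|---|---|---|
| 1.65 | 2.0 | 44% | 48% | 4 |
| 1.65 | 2.5 | 66% | 70% | 4 |
| 2.2 | 2.0 | 39% | 46% | 7 |
| 2.2 | 2.5 | 61% | 69% | 8 |

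With no CT effect, power is 45% either way.

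A smaller simulation (200 trials per setting, treatment OR 2.5, a slightly different assumed GOSE distribution, CT independent of the other covariates) shows where the gain comes from:

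| CT log-odds per SD | Log OR without → with CT | SE without → with CT | Power without → with CT |
|---|---|---|---|
| 0 | 0.950 → 0.956 | 0.382 → 0.384 | 69.0% → 70.5% |
| 0.3 | 0.937 → 0.968 | 0.381 → 0.385 | 71.0% → 71.0% |
| 0.6 | 0.846 → 0.909 | 0.378 → 0.385 | 60.0% → 64.0% |
| 1.0 | 0.841 → 0.960 | 0.377 → 0.390 | 59.5% → 68.5% |

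The standard error does not fall; it rises slightly. The estimate moves away from zero by more, so in the last row the ratio of estimate to SE goes from 0.841/0.377 = 2.23 to 0.960/0.390 = 2.46. With 200 trials each power has a Monte Carlo error of about √(0.65 × 0.35/200) = 0.034, or 3 points, so these powers are only indicative. A further run gave gains of about 2 to 7 points with CT independent of the other covariates, and 2.5 to 5 points with a correlation of 0.4, so overlap lowers the top of the range.

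**Step 4. Chance imbalance.** The standardised baseline difference between arms has SD √(2/48) = 0.20, so 0.4 SD is within the usual range of chance. With an assumed CT–TIL correlation of 0.2 to 0.4, the estimated difference shifts by 0.4 × 0.2 × 3.2 = 0.26 to 0.4 × 0.4 × 3.2 = 0.51 points, or 12% to 23% of the 2.2-point target. The confidence interval already allows for variation of this kind. Adjustment would remove it from the estimate and narrow the interval.

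**The case against.** The strongest reply is that three prespecified baseline covariates are a sound choice and that a reviewer can always propose a fourth. That stands: nothing here is an error.

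A reader might go further and infer any of three things that the article does not support:

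- **That the plan contradicts itself** by promising the strongest predictors and then omitting one. The article does not rank CT against age, GCS and pupils, gives no prognostic figure for midline shift, and ties its set to a cited recommendation that is not shown.
- **That precision is lost on both endpoints.** This is true for TIL only. For GOSE the standard error is no smaller with CT in the model; the gain is in power.
- **That the TIL comparison is biased or underpowered.** It is neither (Step 1). A chance imbalance in an unmodelled covariate is not bias.

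Other parts of the reply also stand. The eligibility criterion requires visible pathology, not a measured shift, and the article does not say that shift on the entry scan is recorded or who would read it. All patients also have invasive ICP monitoring and at least 24 hours of ICP management, which restricts the range of severity. The 12-hour window allows for urgent interventions, so mass effect on the qualifying scan may already have been treated before dosing. GOSE is tested only after a significant TIL result and is not primarily used to declare success.

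These points make the gain uncertain and modest. They do not show a real drawback to adding the covariate: if CT is uninformative, simulated GOSE power is essentially unchanged.

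**Conclusion.** The point holds as a missed efficiency gain, judged against the plan's own two reasons for adjusting. It is a cheap improvement and not the repair of a mistake. For TIL the standard error falls by 0 to about 12% if CT adds an R-squared of 0 to 0.20, and by 3% to 6% if it adds 0.05 to 0.10, on top of power that already exceeds 90%. For GOSE, power rises by about 0 to 8 points, conditional on the gate being passed, and by less if CT overlaps with GCS and pupils.

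All of these sizes rest on assumptions: the prognostic strength of CT, the 0.10 for the existing covariates, the GOSE distribution, treatment odds ratios of 2.0 to 2.5 and, in the tabulated runs, independence of CT from the other covariates.

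**What to change.** In the Statistical analysis section, name midline shift on the qualifying pre-randomisation CT (in mm, or present/absent if only that is available) as a fourth covariate in the TILmax linear model and in the GOSE proportional-odds model. State that it is read blind to allocation. State also that shift seen later in the hospital stay is not used for adjustment, because it arises after randomisation and is itself a secondary outcome. Add this before unblinding, since a covariate chosen afterwards would not be credible.

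The cost is one more parameter in models with about 96 patients and, if entry shift is not already recorded, one baseline field taken from an existing scan. The multiple imputation already planned for missing baseline data would cover scans that cannot be read.

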## Methods

### Trial design

Complement inhibition: Attacking Overshooting inflammation @fter Traumatic Brain Injury (CIAO@TBI) is a multicenter, randomized, blinded, placebo-controlled, phase II trial in patients with TBI. The protocol is designed in accordance with the Standard Protocol Items: Recommendation for Interventional Trials (SPIRIT) 2013 Checklist (Additional file 1) [32]. Patients will be recruited in three-level one trauma centers, including the coordinating neurotrauma research unit of University Neurosurgical Center Holland seated at Leiden University Medical Center (LUMC) and Haaglanden Medical Center (HMC) in close collaboration with Erasmus Medical Center Rotterdam (EMC) and Amsterdam University Medical Centers, location AMC. Patients will be randomized at the ICU in the first 12 h after trauma to receive (1) one dose of C1-INH 6000 IU intravenously (IV) or (2) one placebo injection with 0.9% saline IV.

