### Trial interventions

The intervention is the IV administration of C1-INH compared to a placebo (0.9% saline). A single dose of 6000 IU will be administered within 12 h after trauma. Blood samples (2 EDTA, 1 serum, and 1 citrate tube) will be drawn from both patient groups before administration and at 6, 12, 24, 48, 72, and 96 h after administration of C1-INH or placebo in the ICU. Moreover, if an external venticular drain (EVD) is placed as part of standard care to reduce CSF pressure, additional liquor samples will be drawn before administration and 24, 48, 72, and 96 h after administration of C1-INH or placebo in the ICU. All samples will be centrifuged and aliquoted in 500 μl samples as quickly as possible and afterwards stored at − 80 °C. Other interventions are unaltered from local treatment protocols and will include standard of care in both groups. This might include concomitant therapies, such as a decompressive craniectomy. During hospitalization, patients are closely monitored for (serious) adverse events (SAEs). Moreover, health-related questionnaires will be filled out by the patients or proxies at discharge and at 3 months, 6 months, and 12 months after head trauma. A flowchart of the study design is shown in Fig. 2. All study procedures will be performed according to the designated study operating procedures (SOPs).

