### Primary endpoints

#### Efficacy: Therapy Intensity Level (TIL) Scale

To measure the direct effect on the mechanism of action of C1-INH, our primary endpoint focuses on a decrease in ICP. ICP has been used as a surrogate endpoint for inflammation and testing of neuroprotective agents in many prematurely halted or failed clinical trials [37]. This might be due to the fact that ICP is an early surrogate marker during TBI but confounded by the modern neuro-ICU practices through escalating interventions (such as decompressive craniectomies (DC)) to immediately mitigate surges in ICP resulting in reduction of its sensitivity, as representing “severity of disease.” Therefore, this trial will focus on the intensity of ICP-targeted therapy based on the Therapy Intensity Level (TIL) Scale [38, 39]. The TIL Scale is designed to integrate all known and relevant ICP directed treatments into a single-summary score and was developed as part of the Interagency Common Data Elements scheme [38]. Since its introduction, the novel TIL Scale has been widely used in neurotrauma research, with excellent inter- and intra-rater reliability with minimal measurement errors [39]. The TIL Scale includes eight ICP treatment modalities each with a certain numerical score. Added together, TIL ranges between 0 and 38 points with a right-skewed distribution. Specifically, TBI patients admitted to the ICU have an average TIL score of 8.2 (SD 3.2), while general trauma patients on the ICU have a score of 2.2 (SD 0.9) [39]. The daily score will be calculated based on the highest score in each item per day (TIL24), to provide a metric on the maximal therapeutic intensity for ICP management for that day. The TIL score will be based on the highest TIL24 during the days an ICP monitor is in place (TILmax) and will be scored by a trained research team, and according to an SOP, thereby optimizing inter- and interrater reliability.

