Subgroup analyses on primary outcomes will be performed in the following subgroups: age (< 65 or ≥ 65 years), GCS on admission (moderate and severe TBI), and ICP-directed treatments (high intensity vs. low intensity, secondary DC vs. no secondary DC), and will be presented in forest plots.

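### Two planned subgroups, ICP-treatment intensity and secondary craniectomy, are formed after dosing from what the primary outcome measures, so their forest-plot effects will be biased if C1-INH works

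*Protocol article*

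**What the plan says.** In the protocol article, Statistical analysis: "Subgroup analyses on primary outcomes will be performed in the following subgroups". The list has age (below 65, or 65 and over), admission GCS (moderate, severe) and "ICP-directed treatments (high intensity vs. low intensity, secondary DC vs. no secondary DC", all to be shown in forest plots. The article gives no cut-off for intensity, no time at which it is measured, no definition of secondary DC and no caution about either split.

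Other sections fix the timing and the content:

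- Trial design: "Patients will be randomized at the ICU in the first 12 h after trauma". Trial interventions puts the single dose in the same 12 h.
- Primary endpoints, TIL Scale: "The TIL Scale is designed to integrate all known and relevant ICP directed treatments into a single-summary score", and "The TIL score will be based on the highest TIL24 during the days an ICP monitor is in place (TILmax" is the analysed value.
- The same section names DC among "escalating interventions (such as decompressive craniectomies (DC)) to immediately mitigate surges in ICP".
- Trial interventions, on standard care in both groups: "This might include concomitant therapies, such as a decompressive craniectomy".

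**The concern.** A subgroup analysis estimates a treatment effect only if membership is settled before treatment can influence it. Age and admission GCS meet that condition. Treatment intensity over the monitoring days and secondary DC do not: the trial is powered on the hypothesis that C1-INH lowers the intensity of ICP treatment, that is, that it moves patients from the high to the low stratum.

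Two faults follow. For TIL, the stratifier is the outcome or part of it, so differences within strata shrink because patients who improve leave the stratum. For GOSE and complications, a C1-INH patient who still reaches high intensity or DC tends to be sicker at baseline than a placebo patient who does. The same holds in the low stratum, which takes in C1-INH patients who would have been high on placebo. Randomised comparability is lost in both.

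The article says the results will inform a phase III trial. A forest plot showing little TIL benefit in one stratum, or GOSE odds ratios below 1 in both, could misdirect that trial's eligibility criteria.

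**Working it through.** **Inputs (Sample size section).** Placebo mean TIL 8.2, C1-INH mean 6.0, SD 3.2, 53 per arm, two-sided 0.05, 90% power, about 10% loss. A two-sample t-test needs 45.44, so 46 per arm; 46/0.9 = 51.1, so 52 per arm and 104 in all, against the stated 106. The inputs therefore mean what they appear to mean. Cut-offs, distributions, the DC model and the severity links below are assumptions, because the article gives none.

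**1. TIL split by intensity, closed form (normal, cut c = 8.2).** With a = (c - mean)/SD, the mean above the cut is mean + SD × φ(a)/(1 - Φ(a)), and below it mean - SD × φ(a)/Φ(a).

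- C1-INH: a = (8.2 - 6.0)/3.2 = 0.6875, φ = 0.3150, Φ = 0.7541. High: 10.099. Low: 4.663. In the high stratum: 24.6%.
- Placebo: a = 0, φ = 0.3989, Φ = 0.5. High: 10.753. Low: 5.647. In the high stratum: 50%.
- Differences: high 10.099 - 10.753 = -0.65; low 4.663 - 5.647 = -0.98.
- C1-INH share of the high stratum: 0.246/(0.246 + 0.500) = 33%.

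The rest of the effect is migration between strata. At placebo weights the within-stratum part is 0.5 × (-0.65) + 0.5 × (-0.98) = -0.82. Migration contributes (0.246 - 0.500) × (10.099 - 4.663) = -1.38. Together they give -2.20. The forest plot would hide about 1.4 of the 2.2 points.

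**2. Other distributions and cuts (true difference -2.2 in each; rows 1 and 2 closed form, the rest simulated).**

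| TIL model | Cut | In high: C1-INH / placebo | High | Low |
|---|---|---|---|---|
| Normal | 7.1 | 37% / 63% | -0.80 | -0.80 |
| Normal | 8.2 | 25% / 50% | -0.65 | -0.98 |
| Gamma, SD 3.2 in both arms | 7.1 | 31% / 59% | -0.36 | -1.03 |
| Gamma, SD 3.2 in both arms | 8.2 | 21% / 45% | -0.20 | -1.23 |
| Gamma, every patient shifted by -2.2 | 8 | 24% / 47% | -0.40 | -1.21 |
| Gamma, scaled by 6/8.2 | 8 | 18% / 47% | -1.13 | -0.65 |

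For the normal model and the gamma model with SD 3.2 in both arms, over cuts 6 to 11, the high stratum runs from -0.98 to +0.06 and the low from -0.65 to -1.68. No stratum returns -2.2.

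**3. GOSE with no true effect.** Shifted and scaled gamma models, cuts 7 and 8. GOSE is dichotomised, with log-odds falling by 0.6, 1.0 or 1.5 per SD of baseline severity and no treatment term.

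- Severity-TIL correlation 0.3: C1-INH patients are sicker by 0.10 to 0.18 SD within strata; stratum odds ratios 0.82 to 0.95.
- Correlation 0.6: sicker by 0.21 to 0.36 SD; odds ratios 0.65 to 0.89.

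Every odds ratio is below 1, in both strata.

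**4. Secondary DC.** Normal TIL, P(DC) = 1/(1 + exp(-s × (TIL - 11))), baseline severity explaining 30% or 60% of TIL variance.

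| s | DC rate: C1-INH / placebo | TIL difference, DC | TIL difference, no DC | C1-INH sicker by (SD): DC; no DC |
|---|---|---|---|---|
| 0.3 | 22% / 33% | -1.85 | -1.93 | 0.06-0.08; 0.05-0.07 |
| 0.6 | 12% / 26% | -1.35 | -1.71 | 0.15-0.21; 0.08-0.12 |
| 1.0 | 9% / 22% | -0.90 | -1.61 | 0.22-0.32; 0.10-0.14 |

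At s = 0.6 the DC stratum would hold about 6 C1-INH and 14 placebo patients (12% and 26% of 53).

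**The case against.** - **The primary analysis is untouched.** TIL is tested in all randomised patients and GOSE follows by gatekeeping; the subgroups have no place in that sequence. This stands: sample size, primary estimate and error rate do not change. The article also does not say the forest plots will steer phase III; that is an inference.
- **Timing and content are partly inferred.** The article does not say when intensity is measured, and day-1 TIL can include treatment given before the infusion. It does not list the eight TIL items, so that DC is scored follows from its wording. This stands as a caveat. A pre-dose definition in the full protocol or SAP would cure the intensity split. A cut-off alone would not, and secondary DC as an escalation points to the period after dosing.
- **The bias is conditional.** If C1-INH changes neither TIL nor DC, this bias is absent. True, but a change in TIL is what the trial is powered to find. GOSE is analysed only if TIL differs significantly, so a GOSE subgroup plot would mostly appear when membership has been altered.
- **The figures depend on assumptions.** Which stratum looks weaker depends on the TIL model, the DC split distorts TIL much less, and adjustment for age, GCS and pupils would remove part of the severity imbalance if kept in the subgroup models. This stands for the size. Such adjustment does not repair splitting TIL by itself.

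**Conclusion.** The concern holds. As written, the plan presents two post-dosing variables alongside true baseline subgroups. One is the primary outcome under another name, and the other is a treatment that the outcome score is meant to capture. That overlap is literal for TIL only; for GOSE and complications the fault is conditioning on a variable that treatment affects.

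For a true TIL difference of -2.2, the intensity split shows roughly -0.2 to -1.3 per stratum at cuts of 7 to 8.2, and the DC split roughly -0.9 to -1.9. A null GOSE effect appears as odds ratios of about 0.65 to 0.95 under the intensity split. The sizes rest on assumed cuts and models and are illustrative. In every scenario run, the TIL effects shrank and the C1-INH patients within strata were sicker. The fault lies outside the confirmatory sequence, but should be corrected before any unblinded analysis.

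**What to change.** Change the subgroup paragraph of the protocol, and the matching SAP text, as follows:

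- Keep age and admission GCS, each with a treatment-by-subgroup interaction.
- Remove ICP-treatment intensity and secondary DC from the subgroup list and the forest plots.
- Report secondary DC as an outcome by arm (proportion with a confidence interval). Intensity is already reported by arm as TIL.
- If an intensity contrast is wanted, define it on status before the infusion, for example pre-dose TIL or surgery completed before dosing, and test it as an interaction.
- If patients with DC are to be described, do so in a table outside the forest plots, labelled as not estimating a treatment effect.

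The cost is wording, with no extra patients. Only a pre-dose TIL would add work: the article defines daily and maximum scores only, so a score restricted to the hours before infusion would have to be derived or collected.
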